#### Budget impact analysis

A Budget Impact Analysis (BIA) will be performed in accordance to principles for good BIA practice. A valid framework will be provided according to Markov, leading to insight in budget consequences of desensitization, by a range of predictions based on realistic estimates and scenarios of input parameter values [31]. The likely impact of GMA on center level and also on national health plan budgets.

### Sample size

As the effect size (which varies between Cohen’s *d* = 0.00 and *d* = 0.95) could only be estimated and is best comparable to that shown for cognitive behavioral therapy [32], we presume effect of GMA on endpoints is 0.50 (moderate effect size according to Cohen) [33]. With a power of 0.80 and an alpha of 0.05 (two-tailed), a sample size of 100 patients will suffice (two data sets; children: 40 patients, with 20 in each arm; adults: 60 patients, with 30 in each arm). To adjust for loss to follow up 65 adults and 45 children will be included.

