## Methods/Design

In this RCT with a parallel design, effects of protocolized GMA versus protocolized IMA (care-as-usual) will be tested in SCD patients, over a three year period, for children and adults separately.

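### The stated 80% power does not follow from the stated inputs: for an unadjusted two-tailed comparison, 100 patients give about 70%, and the separate tests about 34% (children) and 48% (adults)

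*Protocol article*

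**What the plan says.** All of the following is in the protocol article.

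- **Sample size.** A moderate effect, Cohen's d = 0.50, is presumed for the endpoints, from a range of 0.00 to 0.95. The conclusion is: "With a power of 0.80 and an alpha of 0.05 (two-tailed), a sample size of 100 patients will suffice". The 100 are divided as "two data sets; children: 40 patients, with 20 in each arm; adults: 60 patients, with 30 in each arm". To allow for loss to follow-up, 45 children and 65 adults are to be included, 110 in all.
- **Methods/Design, opening paragraph.** Effects are to be tested "over a three year period, for children and adults separately".
- **Randomization.** Children and adults are randomised separately, stratified by severity of disease.
- **Outcomes.** The primary endpoint is the self-efficacy score, measured at baseline, 1.5 years and 3 years.

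The Sample size section gives no correlation between measurements, and names no adjusted or repeated-measures model as the basis of the calculation.

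**The concern.** The section prints its inputs (effect, power, alpha, sidedness) and its output (100 patients), and the output does not follow from the inputs. The 80% is also attached to the total, whereas the tests the design describes are made in two smaller data sets.

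If group appointments have exactly the presumed effect, each age-specific unadjusted test is more likely than not to be non-significant. Readers who take the 80% at face value would then give a non-significant result in one age group more weight than it deserves. The Discussion section links wider dissemination to the trial's success, so this misreading could matter.

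**Working it through.** **Inputs, all from the Sample size section:** d = 0.50; alpha 0.05, two-tailed; power 0.80; equal arms; 20 per arm (children), 30 per arm (adults), 50 per arm (total).

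**Step 1. Try to reproduce the 100.** Normal approximation: n per arm = 2(z₁₋α + z₁₋β)² / d², with z for alpha/2 when two-tailed.

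- Two-tailed: 2(1.960 + 0.842)² / 0.25 = 62.8, so 63 per arm, 126 in total. The exact noncentral t gives 63.8, so 64 per arm, **128** in total.
- One-tailed: 2(1.645 + 0.842)² / 0.25 = 49.5, so 50 per arm, 100 in total. The exact t gives 50.15, so 51 per arm, 102 in total.

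The stated two-tailed inputs do not reproduce 100. A one-tailed pooled calculation matches it by the normal approximation and nearly matches it by the exact t.

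**Step 2. Power of the stated numbers.** The noncentrality is d√(n/2), referred to a t distribution with 2n − 2 degrees of freedom, two-tailed 0.05.

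| Data set | n per arm | d√(n/2) | Power at d = 0.50 | d detectable with 80% power |
|---|---|---|---|---|
| Children | 20 | 1.58 | 33.8% | 0.91 |
| Adults | 30 | 1.94 | 47.8% | 0.74 |
| Pooled | 50 | 2.50 | 69.7% | 0.57 |
| Pooled, all 110 analysed | 55 | 2.62 | 73.8% | – |

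Adding an age-group term to the pooled model leaves its power at 69.7%. If all 45 children and all 65 adults were analysed, the separate tests would have about 37% and 51%. One-tailed, at 20 and 30 per arm, they would have 46% and 61%, so sidedness alone does not explain the shortfall.

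**Step 3. What baseline adjustment could add.** The article gives no correlation, so a range is assumed. With one follow-up and a baseline-to-follow-up correlation ρ, the effective effect is d/√(1 − ρ²): 0.546, 0.577 and 0.625 for ρ = 0.4, 0.5 and 0.6.

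| | ρ = 0.4 | ρ = 0.5 | ρ = 0.6 | ρ needed for 80% |
|---|---|---|---|---|
| Children | 39% | 43% | 49% | about 0.84 |
| Adults | 55% | 59% | 66% | about 0.73 |
| Pooled | 77% | 82% | 87% | about 0.47 |

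**Step 4. Using both follow-ups.** Assume an effect of 0.50 at both times and all correlations equal to ρ. The residual variance of the mean of the two follow-ups is (1 + ρ)/2 − ρ². At ρ = 0.5 this is 0.75 − 0.25 = 0.50, an effective effect of 0.50/√0.50 = 0.71. Power is then about 59% (children), 77% (adults) and 94% (pooled). At ρ = 0.6 it is about 64%, 82% and 96%.

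**The case against.** The strongest defence is that the article names no test, that the primary endpoint is measured three times, and that the full protocol or analysis plan may use a baseline-adjusted or repeated-measures model. Steps 3 and 4 show that such a model could bring the pooled comparison to 80% or more at correlations near 0.5. With both follow-ups and a correlation of 0.6, it could bring the adults there too. This stands, and it limits the point: the shortfall is shown for an unadjusted comparison, not for every possible analysis. It does not rescue the paragraph, which invokes no such model or correlation. Children remain below 80% throughout the range of correlations shown.

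A reader might infer more than the article supports:

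- *That a one-tailed test was used by mistake.* The match is close, but a two-tailed pooled test adjusted for baseline at a correlation near 0.5 also reaches about 80% with 100 patients. The origin is not established.
- *That a truly effective intervention would be read as negative.* With the unadjusted powers, and independent groups, the chance that at least one group is significant is 1 − 0.662 × 0.522 = 65%. The chance that both are is 0.338 × 0.478 = 16%.
- *That two tests at 0.05 are an error because 1 − 0.95² = 9.75%.* Children and adults are separately randomised populations. Whether they need joint error control is a matter of preference.
- *That pooling must become the primary analysis.* Separate testing is an explicit design choice. According to the Trial status section, recruitment opened in January 2013 for children and September 2015 for adults, so a pooled primary test would hold back the children's result.

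**Conclusion.** The sample-size statement is wrong as written. At d = 0.50 and two-tailed 0.05, 80% power needs 128 analysed patients in one unadjusted comparison. The 100 planned give about 70%, and the two separate tests about 34% and 48%. The effect that the children's test can detect with 80% power, 0.91, lies close to the top of the range of 0.00 to 0.95 that the article itself quotes.

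These figures assume a two-sample t test, equal arms, the analysed numbers as stated, and an effect standardised by the unadjusted between-patient standard deviation. The adjusted figures rest on assumed correlations, and those for two follow-ups also on an equal effect at both times. The conclusion concerns the printed power claim. It does not show that the trial is bound to miss a real effect.

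**What to change.** 1. Restate the Sample size paragraph. Give the two-tailed power at d = 0.50, or the effect detectable with 80% power, for children, for adults and for the total. Drop the claim that 100 patients give 80% power.
2. Analyse self-efficacy in each age group adjusted for its baseline value and for the severity stratum already used in randomisation. If adjusted power is quoted, state the assumed correlation and the number of follow-ups it uses; the tables above give the range.
3. Optionally, add a pooled estimate adjusted for age group, with an arm-by-age-group interaction. It need not replace the separate analyses, and it presumes that the self-efficacy score is comparable across ages, which the sponsor should confirm.

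The cost is a rewritten paragraph and a specified covariate set. No extra patients are needed. The downside is that the stated power becomes less favourable, above all for children.

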### Randomization

After informed consent, patients (children and adults separately) will be randomized by the investigator with the use of the Trial Online Process registration and randomization program. Allocation will be known to all involved in the study. The randomization process will stratify by severity of disease (with severe SCD defined as: HbSS or HbSβ0 and milder disease defined as: other compound heterozygous forms of SCD). In order to investigate whether the study population is a representative sample of the total population in our hospital we will compare background variables (age, gender, socioeconomic status and diagnosis) between both populations when the study is completed.

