### Outcomes

Primary and secondary endpoints will be measured at baseline (start of the study), after 1.5 years (after two GMA visits) and after 3 years (after four GMA visits), in both groups. Assessments are performed at the hospital, directly before the outpatient visit and in presence of a psychologist.

Primary endpoint:Self-efficacy as measured by the validated Sickle Cell Self- Efficacy Scale [7];

Secondary endpoints:2.Adherence to prescribed treatment by (pediatric) hematologist, defined by:Self-report (Morisky Medication Adherence Scale) [23];Variations in adherence (Medication Adherence Report Scale) [24];Blood values suggesting adherence to prescribed medication (folic acid, hydroxycarbamide, iron chelation therapy) such as: folic acid (nmol/l), MCV (fl), fetal hemoglobin percentage (HbF %), ferritine (mcg/l);Attendance at outpatient clinic visits or imaging examinations (% of total planned).3.Quality of life as measured with the validated Pediatric Quality of Life Inventory for children [25] and SF-36 for adults [26].4.Emergency visits and hospital admissions for SCD related symptoms and complications. At *t* = 0, morbidity of preceding 3 years will be measured as baseline. All patients in the study will receive a dossier in which sickle cell crises, emergency department visits, hospital admissions, blood transfusions will be documented.5.Satisfaction with treating physician and nurse (by visual analogue scale: score 1–10) [27, 28].6.Measurement of costs and effects in the GMA and IMA group by an economic analysis according to Dutch guidelines and with respect to an increase in self- efficacy.

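### The stated 100 patients do not give 0.80 power at d = 0.50, least of all in children and adults tested separately; adjusting for baseline self-efficacy and severity is a partial remedy only

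*Protocol article*

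**What the plan says.** In Sample size, the protocol article sets the effect: "we presume effect of GMA on endpoints is 0.50 (moderate effect size according to Cohen". It continues: "With a power of 0.80 and an alpha of 0.05 (two-tailed), a sample size of 100 patients will suffice". The 100 are then divided into two data sets: "children: 40 patients, with 20 in each arm; adults: 60 patients, with 30 in each arm". Recruitment is raised slightly for attrition: "To adjust for loss to follow up 65 adults and 45 children will be included". The section mentions no covariate, baseline correlation or variance reduction. It does not say whether the 0.50 is standardised on raw, change or baseline-adjusted scores.

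Methods/Design says that effects will be tested "over a three year period, for children and adults separately".

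In Outcomes, the primary endpoint is "Self-efficacy as measured by the validated Sickle Cell Self- Efficacy Scale", and "Primary and secondary endpoints will be measured at baseline (start of the study), after 1.5 years" and again after 3 years.

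In Randomization, children and adults are randomised separately and "The randomization process will stratify by severity of disease", in two levels defined by genotype.

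The article names no analysis model for the primary endpoint.

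**The concern.** The total of 100 does not follow from the effect size, alpha, sidedness and power given beside it. The gap widens once the 100 are split into two data sets that are each tested. A reader who takes the 0.80 at face value would treat a null result in children or adults as fairly strong evidence against a moderate effect. With one chance in three (children) or one in two (adults) of detecting that effect, a null result would say little.

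The trial already holds two sources of precision that the calculation does not use: the baseline score on the primary scale and the severity stratum. If severity predicts self-efficacy, an analysis that leaves out the stratum after stratified randomisation also gives a standard error that is too large. How much of the shortfall adjustment can repair must be worked out for the analyses the protocol plans, not only for all 100 together.

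**Working it through.** **Inputs from the article.** d = 0.50; two-sided alpha 0.05; target power 0.80; n per arm 20 (children) and 30 (adults), so 50 if pooled. **Assumed, not in the article:** the correlation r between baseline and 3-year self-efficacy, shown for 0.3, 0.5 and 0.7; and the share of outcome variance explained by severity, shown for 5% and 10%.

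**1. The plan's own figure.** Normal approximation, per arm:

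n = 2(1.960 + 0.842)² / 0.50² = 8 × 7.85 = 62.8, so 63 per arm (126 in total).

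With the t distribution it is 63.8, so 64 per arm (128 in total). The figure of 100 is not reproduced. The only variant tried that gives it is one-sided and pooled: 8 × (1.645 + 0.842)² = 49.5, so 50 per arm. That conflicts with two-tailed testing and with separate testing.

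**2. Unadjusted power at the stated sizes.** Noncentral t with noncentrality d√(n/2) and 2n − 2 degrees of freedom:

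| Data set | n per arm | Noncentrality | Power | Detectable d at 0.80 |
|---|---|---|---|---|
| Children | 20 | 1.581 | 34% | 0.91 |
| Adults | 30 | 1.936 | 48% | 0.74 |
| Pooled | 50 | 2.500 | 70% | 0.57 |

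If all 45 children and 65 adults were retained, power would be 38%, 51% and 74% (pooled), so the attrition allowance does not explain the gap.

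**3. Adjusting for baseline and stratum.** Baseline adjustment multiplies the residual SD by √(1 − r²), so the noncentrality becomes d√(n/2) / √(1 − r²). Degrees of freedom are 2n − 4 (baseline and stratum). No variance is credited to the stratum here. Example for children at r = 0.5: 1.581 / 0.866 = 1.826 on 36 degrees of freedom, critical value 2.028, power 43%.

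| Data set | r = 0.3 | r = 0.5 | r = 0.7 | r needed for 0.80 |
|---|---|---|---|---|
| Children | 36% | 43% | 58% | 0.84 |
| Adults | 51% | 59% | 76% | 0.73 |
| Pooled | 74% | 82% | 93% | 0.47 |

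Adding age group to the pooled model costs one more degree of freedom and leaves these figures unchanged at this rounding.

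**4. Share of the shortfall recovered,** (adjusted − unadjusted) / (0.80 − unadjusted), at r = 0.3 / 0.5 / 0.7: children 6% / 19% / 52%; adults 11% / 36% / 87%. Children at r = 0.5: (0.428 − 0.338) / (0.80 − 0.338) = 0.19.

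**5. Stratum alone.** If severity explains 5% or 10% of the variance, power becomes 35% or 37% in children, 50% or 52% in adults, and 72% or 74% pooled. That is a gain of 1 to 5 points.

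**The case against.** The strongest reply is that the article names no analysis model. A baseline-adjusted or repeated-measures analysis may be specified in a full protocol or SAP that is not shown, and three assessments are compatible with either. Sizing a trial without a covariate term is also a common, cautious choice when the correlation is unknown, and stratifying by severity is sound. All of this stands. The absence of a model is not a fault here, and a reader who infers that an unadjusted analysis is planned goes further than the text. But the sentence on power is stated in the article and is wrong on its own inputs, whatever the SAP contains. Nor is it cautious: the unadjusted calculation reaches 70% at best.

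A second tempting reading is that adjustment costs nothing and recovers most of the missing power. The documents do not support it. They give no correlation, and in the data sets to be tested, r = 0.5 recovers only about a fifth (children) or a third (adults) of the shortfall. The claim works only for one analysis of all 100. Adding age group as a covariate would turn two planned tests into one. That changes the question: the two groups have different care teams and their recruitment opened more than two years apart.

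Third, if d = 0.50 is already on an adjusted or change scale, adjustment would bring less further gain than shown. The article leaves this open.

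**Conclusion.** The concern holds in this form: the power statement in Sample size is wrong. At d = 0.50 and two-sided 0.05, unadjusted power is about 34% in children and 48% in adults, against the stated 0.80, and about 70% even if pooled. These figures rest only on the article's own numbers, reading d as a plain standardised difference between arms.

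Adjusting for baseline self-efficacy and severity is worthwhile and uses data already planned, but it is a partial remedy whose size depends on an assumed correlation. For r from 0.3 to 0.7, it leaves children at 36% to 58% and adults at 51% to 76%. Neither planned test reaches 0.80 in that range. A pooled analysis does from about r = 0.47, but the article does not plan one.

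**What to change.** 1. In Sample size, withdraw the claim of 0.80 power at d = 0.50 from 100 patients. State instead the power of each separate analysis (about 34% and 48% unadjusted) or the detectable effect at 0.80 power (about d = 0.91 in children and 0.74 in adults; 0.57 if pooled). Say on which scale d is standardised.
2. Within each data set, analyse 3-year self-efficacy by arm, adjusted for baseline self-efficacy and severity stratum (HbSS or HbSβ0 versus other). If the SAP already does this, refer to it. Give the power for that model with the assumed correlation and its range.
3. If a pooled analysis of all 100 with age group as a further covariate is wanted, state it explicitly as an additional analysis, with its assumption of a common effect. It should not silently replace the separate tests.

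Items 1 and 2 cost only protocol and SAP wording: no extra patients, visits or measurements, and two degrees of freedom per data set. Item 3 costs more, because it adds a different question. The article describes the trial as still ongoing, so these changes should be dated and made before outcome data are examined, since allocation is open. Keeping 0.80 power at d = 0.50 without adjustment would need about 64 per arm in each data set, or 256 patients (2 × 128), against the 110 to be enrolled.

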## Discussion

This article presents the rationale and design of a RCT to test the effectiveness of GMA versus IMA on self-efficacy, adherence, quality of life and patient-professional relationship in pediatric and adult patients with SCD. Furthermore, effects of GMA on medical costs (e.g., morbidity, hospital admissions) will be tested. This is the first study to investigate the effects of GMA on these parameters in patients with SCD and is the first to evaluate the cost-effectiveness of such an intervention. If the GMA’s prove successful in improving self-efficacy, adherence and cost-effectiveness, this innovation in SCD care may be disseminated at an (inter)national level.

## Trial status

The trial opened to recruitment in January 2013 for the children and in September 2015 for the adults and is still ongoing.

## Abbreviations

BIA, budget impact analysis; CBO, Kwaliteitsinstituut voor de Gezondheidszorg; GMA, group medical appointment; ICER, incremental cost-effectiveness ratio; IMA, individual medical appointment; RCT, randomized controlled trial; SCD, sickle cell disease
